### Power and sample size calculation

In our previous RCT, comparing VRcbt with waiting list, the effect size on Ecological Momentary Assessment (EMA) paranoid delusions (see primary outcome measures) was 1.6 [15]. In the current study, the effect size is likely to be smaller with standard CBTp as active control condition. Assuming a much lower but still clinically relevant effect size of 0.6, a sample size of 122 (allowing 15% drop-out) will have a power of 80% to detect a multically significant treatment effect, using an alpha of 0.05 and a standard deviation of 1.1 for the outcome measure. Taking the multilevel structure of the data into account, with a (conservative) intra correlation coefficient of 0.8 and a commonly applied multiplication factor [20], 106 participants are needed for a unilevel equivalent *N* = 122.

### Interventions

#### VRcbt

VRcbt will be delivered by trained therapists, with at least a postgraduate qualification in CBT, and with a minimum of half a year of experience in psychosis treatment.

VRcbt consists of maximum 16 sessions within an 8–12-week time-frame. Sessions will last maximum 75 min, of which 40 min are spent in virtual social situations that trigger paranoid delusions and distress. The remaining time will be used to plan and reflect on exercises and to complete the session measurements. Throughout the first sessions, therapists construct individually tailored case-formulations based on CBTp, in close collaboration with the patient in order to create a shared understanding of the current paranoid ideas, related feelings and behaviour. Subsequently, patients are guided by therapists who help them drop safety behaviours and test their paranoid beliefs. The following animated virtual social environments can be used, i.e., café, shopping street, supermarket, bus ride, office and living room. The level of difficulty of the particular social environment can be modified by adjusting the number, gender and ethnic appearance of virtual characters (avatars) present in the situation. The level of hostility and suspicious behaviour can be modified as well. Personalized interactive scenarios can be role-played. The therapist talks via a microphone (with voice distortion) as an avatar and operates the avatars’ body movements. Patients wear an Oculus Rift head-mounted display and navigate through the virtual environments using a controller.

#### CBTp

CBTp will be delivered by trained therapists, with at least a postgraduate qualification in CBT, and with a minimum of half a year of experience in psychosis treatment. CBTp also consists of maximum 16 sessions which last up to 75 min within an 8–12 week time-frame. CBTp emphasises cognitive techniques, such as cognitive restructuring and behavioural interventions, including exposure and behavioural experiments. CBTp focuses on exercises aimed at reappraisal of paranoid beliefs’ meaning to reduce distress and improve coping in daily life. Throughout the first sessions, therapists construct individually tailored case-formulations based on CBTp, in close collaboration with the patient in order to create a shared understanding of the current paranoid ideas, related feelings and behaviour. Each session, time will be reserved for planning and reflecting on exercises and completing the session measurements. The Dutch CBT protocol for delusions will be applied (gedachtenuitpluizen.nl).

### Treatment quality and fidelity

Both interventions will be delivered by the same therapists, who are trained in both protocols. All therapists are supervised by a highly skilled and experienced mental health care professional with a registration at the Dutch Association of Behavioural and Cognitive Therapy (VGCt). The VGCt is the scientific association for cognitive-behavioural therapists in the Netherlands. The VGCt is committed to high-quality and scientifically sound development and practice of cognitive-behavioural therapy. For each participant, therapists write a individually tailored case conceptualisation, guided and evaluated after session two by the supervising psychologist. The treatment can only continue after approval of the case conceptualisation. In addition, therapists participate every month in 2-h group supervision sessions, both for VRcbt and CBTp, during which ongoing treatments are presented and discussed. Supervisors meet in online sessions every six weeks. All treatment sessions are audio recorded. A selection of treatment sessions will be rated for treatment fidelity, using the Cognitive Therapy Rating Scale (CTRS) [21]. The CTRS [21] is a reliable [21] and valid [22] instrument to measure treatment fidelity when following a CBTp protocol.

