### Randomization and allocation concealment

Randomization will occur after completion of the baseline assessment. Block randomization will be used, with a block of eight random assignments for each participating mental health centre. The allocator will hide block size from the therapist and research assistants to prevent prediction of the next assignment. After a mental health centre has included eight patients, new blocks will be made available. Allocation to the two conditions will be in a 1:1 ratio. Randomization will be carried out by using the online randomization program www.randomizer.org by an independent researcher of the University Medical Center Groningen who is not involved in the trial. After the baseline assessment, the first author will enter the patients study ID into the online service and receive an email that details the patient’s allocation. The first author will then contact the therapist to inform them of the patients’ allocation. The therapist will then contact the patient about the allocation and to arrange the first therapy session.

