#### Data analysis

Analysis will be performed according to the intention to treat principle. The groups will be compared at baseline. In case of baseline differences, variables will be added to further analyses as covariates. Potential covariates include age, sex, duration of illness and medication. The effect of VRcbt will be analysed by random intercept mixed effects regression models. The fixed effect of interaction between treatment group (VRcbt or CBTp) and time on momentary paranoia will be fitted as an estimate of the VRcbt treatment effect. Mean scores before and after treatment on each of the dependent variables will be compared between conditions. To determine the number of sessions needed for achieving clinically meaningful change, scores of patients on the VAS, the SDS and the GCI will be compared between conditions. The standard error of measurement (SEM) will be used to determine the proportion of participants with clinically meaningful change in each condition at each time point. Furthermore, cost-effectiveness analyses (CEA) will be conducted using the TiC-P and the EQ-5D-5L questionnaire. The economic evaluation consists of a CEA with improved momentary paranoia in daily life situations and a cost-utility analysis (CUA) with quality-adjusted life years (QALYs) gained as outcome. For both analyses, the incremental cost-effectiveness ratio (ICER) will be calculated as the between-group cost difference divided by the between-group effect difference. The ICER represents the additional costs needed (or saved) for establishing the VRcbt effect. The cost-utility ratio does the same per additional QALY gained. To handle uncertainty in the cost and effect data, nonparametric bootstrapping will be conducted to simulate 2500 ICERs.

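### One therapist pool serves both arms, but no step ties patient to therapist before allocation and the stated model omits therapist; the error bars can be too narrow if therapists differ by treatment or are chosen by arm

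*Protocol article*

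**What the plan says.** All places are in the protocol article.

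- Treatment quality and fidelity: "Both interventions will be delivered by the same therapists, who are trained in both protocols". Therapist is therefore crossed with arm by design.
- Randomization and allocation concealment: "Block randomization will be used, with a block of eight random assignments for each participating mental health centre". Centre is the only stratum. Once the allocation is out, "The first author will then contact the therapist to inform them of the patients’ allocation". That section says when a therapist is told. It does not say when that therapist was chosen.
- Data analysis: "The effect of VRcbt will be analysed by random intercept mixed effects regression models", without naming the level of the intercept. On the effect estimate: "The fixed effect of interaction between treatment group (VRcbt or CBTp) and time on momentary paranoia will be fitted". On adjustment: "Potential covariates include age, sex, duration of illness and medication". Therapist is in none of these.
- Power and sample size calculation: the only correlation used is 0.8. The working shows that it fits repeated measures within a patient, so no allowance is made for therapist.

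**The concern.** The two treatments ask different things of a therapist. In VRcbt the therapist speaks as the avatar, moves it and sets how hostile the scene is. CBTp rests on cognitive restructuring and behavioural experiments without that apparatus. A therapist may do better with one than with the other. Patients of that therapist in the same arm then share part of their change, and a model without therapist treats them as independent.

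The second route is the choice of therapist. If a centre could pick the therapist once the arm is known, VR patients might go to the therapist keenest on VR. Part of the arm difference would then be a difference between therapists.

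The stake is whether the interval and p-value describe VRcbt against CBTp or lean on the particular therapists who took part.

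**Working it through.** **1. The plan's own figure.** Inputs from Power and sample size calculation: difference 0.6 ("Assuming a much lower but still clinically relevant effect size of 0.6", which reproduces only as a raw difference), SD 1.1, alpha 0.05 (taken as two-sided), power 80%, drop-out 15%, correlation 0.8.

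- Per arm: 2 × (1.96 + 0.84)² × 1.1² / 0.6² = 52.8, so 53, or 106 in total.
- Drop-out: 106 × 1.15 = 121.9, so 122.
- Multilevel factor for three occasions (T0, T1, T2): (1 + 2 × 0.8)/3 = 0.867, and 122 × 0.867 = 105.7, so 106.

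The stated 122 and 106 reproduce, and the 0.8 is used up by the three occasions. Nothing is added for therapist.

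**2. Effect of leaving therapist out.** The article gives neither the number of therapists K nor any therapist variance, so these are assumptions. Take one change score per patient with total variance 1, N = 106, therapist main-effect share ρ and therapist-by-arm share g. With equal caseloads there are m = 106/(2K) patients per therapist and arm.

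- Crossed: (true SE / model SE)² = (1 − ρ − g) + g × m.
- Fully separated by arm: (true SE / model SE)² = 1 + (106/K − 1) × ICC.
- Actual type I error of a nominal 5% test = 2 × [1 − Φ(1.96 / SE ratio)].

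Example, K = 8, ρ = 0.05, g = 0.05: m = 6.625, and 0.90 + 0.05 × 6.625 = 1.231. The SE ratio is 1.11 and type I error is 7.7%.

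Type I error from these formulas, with ρ = 0.05 in the crossed columns and ICC = 0.05 in the last:

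| K | main effect only | g = 0.02 | g = 0.05 | separated by arm |
|---|---|---|---|---|
| 8 | 4.4% | 5.7% | 7.7% | 12.3% |
| 12 | 4.4% | 5.2% | 6.4% | 9.7% |
| 20 | 4.4% | 4.8% | 5.4% | 7.5% |
| 30 | 4.4% | 4.6% | 4.9% | 6.5% |

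**3. Simulation without equal caseloads.** Same shares, no therapist term, 12,000 runs per cell, K from 8 to 30. The crossed ranges cover patients spread over therapists at random and caseloads made markedly unequal (Dirichlet, parameter 2).

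- Main effect only: 4.7 to 5.4%.
- g = 0.02: 5.5 to 7.2%.
- g = 0.05: 5.8 to 10.6%. The top is 8 therapists with unequal caseloads.
- Separated by arm, ICC 0.05, random caseloads: 6.9 to 13.0%.

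Partial separation does less. With half of the patients routed by arm and ICC 0.05, a separate simulation gives 6.5% for 10 therapists and 5.4% for 20.

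**4. What a therapist intercept alone would do.** With a main effect only and each therapist treating equal numbers in both arms, it removes a share ρ of the variance. With 53 per arm, 0.6 / (1.1 × √(2/53)) = 2.81, which gives power 80.2%. Dividing 2.81 by √0.95 or √0.90 gives 2.88 or 2.96, so power of about 82% or 84%. That is a gain in precision. It does not touch g.

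**The case against.** Three points can be made for the plan.

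**The crossed design protects the comparison.** A reader might infer that leaving therapist out must make the error bars too narrow. The documents do not support that. When each therapist treats in both arms, a shared therapist effect largely cancels, and the check gives about 4 to 5% with a main effect only. The article also requires training in both protocols, monthly supervision, approval of each case conceptualisation and fidelity ratings of a selection of sessions. This stands. These measures may reduce therapist-by-arm differences, but they do not show that there are none.

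**Choice of therapist after allocation is not stated.** A reader might infer it from the order of events in Randomization and allocation concealment. That text describes notification only, and its wording fits a therapist already identified. This stands too: the route is left open, not described. Full separation by arm would also contradict Treatment quality and fidelity.

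**An unseen analysis plan may name further random terms.** This is a fair limit on the modelling half, since the article is condensed and its intercept level is unnamed. It does not reach the other half. When the therapist is named relative to allocation is a matter of trial conduct, and an analysis plan cannot supply it afterwards.

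**Conclusion.** The concern holds in a conditional form, as a low-cost improvement. The article fixes no therapist before the allocation is released and names no therapist term. With a common therapist effect alone, the test stays at about 4 to 5%. Under therapist-by-arm variation with a share of 0.02 to 0.05, it rejects about 5 to 10% of the time. If therapists separated by arm at ICC 0.05, the figure would be about 7 to 12%.

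These sizes rest on an assumed 8 to 30 therapists, assumed variance shares and assumed caseloads. With 20 or more therapists and equal caseloads, the crossed inflation is close to nil. The documents neither state nor rule out either of the two mechanisms, so a certain understatement of the standard error cannot be claimed.

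**What to change.** 1. In Randomization and allocation concealment, have the centre record the intended treating therapist on the randomisation request before the allocation is released, and log any later change with its reason. If the choice did follow the arm, no later model could fully repair it.
2. In Data analysis, add a therapist random effect on change with a therapist-by-arm component. If that component cannot be estimated, report therapist-clustered standard errors with a small-sample correction as a sensitivity analysis. A therapist intercept alone may be added for precision, but it should not be presented as protection against therapist-by-arm variation.

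The cost is one form field, one model term and a slightly wider interval if therapist-by-arm variation exists. No extra patients or visits are needed.

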### Materials and measurement instruments

#### Primary outcome measure

##### Momentary paranoia in daily life social situations

Level of momentary paranoia in daily life is measured with *Ecological Momentary Assessment* (EMA). EMA is a structured diary method in which patients are asked to report their momentary thoughts, feelings and symptoms, as well as the (appraisal of the) social context in daily life [23]. Momentary paranoia is measured ten times a day for seven consecutive days before treatment, after treatment and three months after treatment. Items assessing momentary paranoia include “I feel that others might hurt me”, “I feel that others dislike me” and “I feel suspicious” [24]. Items are scored on a 7-point Likert scale ranging from 1 (not at all) to 7 (very). Mean total scores are calculated based on all 70 measurements. The EMA allows investigation of experiences occurring in daily life environments instead of retrospective self-reflection on feelings and behaviour [25]. Therefore, the EMA is less sensitive to recall bias and has a high ecological validity [23].

### Secondary outcome measures

#### Social participation

Social participation is measured by means of EMA. Social participation items assess level of social activities, and proportion of time spent in social company in a natural flow and setting of daily life.

##### Paranoid thoughts

The *Green Paranoid Thoughts Scale* (GPTS) [19] is a self-report questionnaire that consists of two subscales each including sixteen items: part A measures paranoid delusions of social reference and part B measures social persecution, in the past month on a five-point Likert scale. Both scales and their dimensions have good internal consistency and validity [19].

##### Paranoid delusions and hallucinations

The *Psychotic Symptom Rating Scales* (PSYRATS) [26] are semi-structured interviews designed to measure the subjective characteristics of hallucinations and delusions. The PSYRATS has good inter-rater and retest reliability and has good validity, as assessed by internal consistency, sensitivity to change, and in relation to the PANSS [26].

##### Social anxiety

The *Social Interaction Anxiety Scale* (SIAS) [27] consists of nineteen items assessing fear of general social interaction, i.e. distress when meeting and talking with other people, on a five-point Likert scale. High levels of internal consistency and test-retest reliability were established for both scales [27, 28].

##### Depressive symptoms

The *Inventory of Depressive Symptomatology Self-Report* (IDS-SR) [29] is a 30 items self-report questionnaire assessing severity of depressive symptomatology in the past seven days. Psychometric properties of IDS-SR are satisfactory and the instrument has been recommended in research [29, 30].

##### Safety behaviour

The *Safety Behaviours Questionnaire – persecutory delusions* (SBQ) [31] is a semi-structured interview designed to measure safety behaviours, i.e. actions with the aim of reducing persecutory threat. In case a safety behaviour has been reported a patient is asked to rate its frequency over the past month on a four-point scale. The SBQ has a high inter-rater reliability, and an adequate test-retest reliability. The SBQ has adequate validity [31].

##### Worry

The *Penn State Worry Questionnaire* (PSWQ) [32] is a 16-item self-report questionnaire which assesses the trait pathological worry on a five-point scale. The PSWQ has proven to be a reliable and valid measure [32].

##### Self-esteem

The *Self Esteem Rating Scale – Short Form* (SERS-SF) [33], has been designed to measure self-esteem by means of a positive and negative self-esteem subscale. The instrument is a self-report questionnaire that contains 20 items using a seven-point Likert scale. The SERS-SF has shown to be a reliable and valid instrument [33].

##### IPSM

The *Interpersonal Sensitivity Measure* (IPSM) [34] is a self-report questionnaire developed to measure hypersensitivity to interpersonal rejection. The IPSM yields a total score as well as five subscale scores: interpersonal awareness, need for approval, separation anxiety, timidity and fragile inner-self. The IPSM has good psychometric properties [34, 35].

##### Cognitive schemas

The *Brief Core Schema Scales* (BCSS) [36], a 24-item self-report questionnaire, assesses schemata concerning the self and others on four dimensions (negative-self, positive-self, negative-other and positive other) on a five-point Likert scale. The BCSS has good psychometric properties including construct validity [36].

##### Cognitive biases

The *Davos Assessment of Cognitive Biases* (DACOBS) [37] is a self-report questionnaire which assesses cognitive problems and biases on seven independent subscales (jumping to conclusions, belief inflexibility bias, attention for threat bias, external attribution bias, social cognition problems, subjective cognitive problems and safety behaviour) in the past two weeks on a seven-point Likert scale. The DACOBS has proven to be a reliable and valid measure for use in clinical practice and research [37].

#### Cost-effectiveness and cost-utility

##### Healthcare and productivity costs

The *Trimbos Institute and Institute of Medical Technology Assessment questionnaire for Costs associated with Psychiatric illness* (TiC-P) [38] is a self-report questionnaire assessing direct medical costs and productivity costs due to absence from work or reduced efficiency during paid or unpaid costs. The psychometric properties of the TiC-p are satisfactory [38].

##### Quality of life

The *EuroQol Five Dimensions Five Levels* (EQ-5D-5L) [39] is a health related self-report questionnaire which assesses quality of life on five dimensions: mobility, self-care, usual activities, pain/discomfort, and anxiety/depression. Each dimension is rated on a five-level scale that describes the extent of problems in that area. Participants also rate their overall health on the day of the assessment on a 0–100 visual analogue scale (EQ-VAS). The EQ-5D-5L has shown improvement of psychometric properties in relation to the EQ-5D-3 L [40].

##### Clinically meaningful change

In order to test differences between VRcbt and CBT in number of sessions needed to achieve clinically meaningful change, Visual Analogue Scales (VAS), the Sheehan Disability Scale (SDS) [41] and the Clinical Global Impressions Scales (CGI) [42] are used. Patients-ratings on the VAS in combination with SDS will be administered at the beginning of each session, and clinician-ratings on the CGI will be administered at the end of each session. The *Visual Analogue Scales* (VAS) consists of nine items extracted from the GPTS [19], which assesses paranoid thoughts and delusions.

The *Sheehan Disability Scale* (SDS) [41] is a patient-rated measurement on a ten-point scale designed to assess functional impairment in three inter-related domains: work/school, social and family life. The SDS is a psychometrically sound instrument [41]. The *Clinical Global Impression Scale* (CGI) [42] is a brief clinician-rated measurement on a 7-point scale assessing overall symptom severity (i.e. severity of complaints of paranoia safety behaviour and social avoidance) and global improvement (i.e. overall comparison of the patients baseline condition to a ratio of current therapeutically benefit). The CGI applied to schizophrenia has proven to be a valid and reliable instrument to evaluate severity and treatment response [43].

#### Other

##### Presence

The *Igroup Presence Questionnaire* (IPQ) [44] is a fourteen-item self-report questionnaire using a seven-point Likert scale, designed to measure the sense of presence experienced in a virtual environment. The IPQ has established good psychometric properties [44] **Social functioning** The *Personal and Social Performance Scale* (PSP) [45] is an interview designed to assess the extent of disability (1 absent – 5 severe) in four components of social functioning (meaningful activities, personal and social relationships, self-care, and disturbing and aggressive behaviour). The ratings of each component are combined into one score from 0 to 100. The PSP has shown to be a reliable and valid measure [45]. **Demographic background** The questions regarding demographic information include level of education, ethnicity, age, gender, substance use (alcohol, tobacco, cannabis and illicit drugs) and use of medication (antipsychotics, benzodiazepines, other psychotropic drugs).

